### Treatment adherence

Treatment adherence (number of sessions attained) will be prospectively documented by the treating PT in a logbook. For the home-based exercise program, participants will record number of training sessions and perceived training intensity on a Borg-scale [51] in a logbook.

### Other process measures

Feasibility: The drop-out rate, defined as the proportion of participants who discontinue their participation before completing the study protocol, will be determined by the number of participants who provide informed consent but fail to complete the follow-up assessments at the predefined end point (e.g., 8 weeks). Reasons for drop-out will be recorded where available (e.g., adverse events, loss of motivation).User satisfaction with Reforter™ system will be assessed with the Net Promoter Score (NPS) [52], a single-item questionnaire asking participants to rate the likelihood of recommending the Reforter™ system to others on a scale from 0 (not at all likely) to 10 (extremely likely).

### Adverse events

Adverse events or side effects of the training program will be prospectively documented by the treating PT in a logbook.

### Intervention fidelity

To monitor treatment fidelity, physiotherapists will complete customized semi-structured notes in a logbook for each treatment session. The research staff will regularly review these notes to ensure that the intervention is delivered according to the study protocol, including appropriate progression in exercise intensity.

### Trial sample size

This study was designed as an exploratory mechanistic trial because no previous studies have compared strength and endurance exercise in patients with RA, OA or SARC. Consequently, no reliable disease-specific between-group effect size was available to perform a formal a priori sample size calculation for the primary comparison. The target sample size was therefore determined pragmatically, balancing the feasibility of the extensive mechanistic assessments (including muscle biopsies, mitochondrial respirometry and inflammatory biomarker analyses) with the aim of including as many participants as possible within the available resources and study period. A total of 69 patients will be included, taking into account a 15% dropout rate, 60 patients will be analysed of which 30 will be randomized to the strength group and 30 to the endurance group, stratified by diagnosis (OA, SARC and RA) and gender. This resulted in a target sample size of 69 participants (23 per disease group). The study is intended to estimate intervention effects, variability and mechanistic associations to inform the design of future adequately powered confirmatory studies. The study is not powered for separate confirmatory analyses within each disease group.

### Data management

Each participant will be assigned a unique study identification code to ensure confidentiality. Personal identifying information will be stored separately from research data and will only be accessible to the principal investigator and authorized members of the research team. All study data will be collected and processed using this coded identifier.

Clinical data will be collected by a trained researcher at Reade and recorded in electronic case report forms in Castor EDC at Amsterdam UMC. Data related to muscle biopsies and laboratory analyses will be collected and stored at Amsterdam UMC. Treatment adherence, training intensity, and adverse events will be recorded by the treating physiotherapists in standardized logbooks. These data will subsequently be entered into the electronic case report forms in Castor EDC by a member of the research team. All study data will be stored on secure, password-protected institutional servers at Amsterdam UMC and Reade, in accordance with institutional data protection policies.

Data quality will be ensured through predefined data entry checks and periodic monitoring procedures. Source data verification will be performed on a sample of records and focused on key study variables, informed consent documentation, and protocol adherence.

Study data will be retained for a minimum of 15 years after completion of data collection, in line with institutional and regulatory requirements. De-identified data underlying the findings of this study will be made available upon reasonable request, subject to ethical approval and data protection regulations.

### Data analysis plan

Descriptive statistics will be used to analyze the participant characteristics including sociodemographic variables (e.g., age, sex, educational level, living situation, smoking, alcohol consumption), clinical factors (e.g., diagnosis, comorbidities, medication use), anthropometric measures (e.g., BMI, muscle mass), and baseline outcome variables. Muscle-related characteristics will be grouped and described according to their physiological domain (e.g., muscle morphology, muscle strength, mitochondrial function and blood biomarkers). Analyses will be performed for baseline and baseline compared to follow-up (delta muscle strength). Analyses will encompass calculations of means (SD)/ median [IRQ], scatterplots and covariance matrices, stratified by diagnosis and gender and with respect to main study endpoint.

#### 1. Primary outcome (isokinetic muscle strength).

The effect of exercise type (strength vs. muscle endurance exercise) on isokinetic muscle strength (pre- vs. post-intervention) will be assessed using linear mixed models. Models will include fixed effects for exercise group, time (pre/post), exercise group, disease type, and gender. The time × exercise group interaction will be included to estimate differential changes in muscle strength between intervention groups. Random effects will account for individual variability.

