## Abstract

**Objective:**

Muscle weakness is prevalent in rheumatoid arthritis (RA), osteoarthritis (OA) and sarcopenia (SARC). Endurance exercises may improve mitochondrial function and oxidative capacity, while strength exercises are thought to stimulate myofibrillar protein synthesis. This study aims to compare the effects of strength and endurance exercise and explore the association between muscle characteristics and exercise outcomes in patients with RA, OA and SARC. We hypothesize that responses to endurance and strength exercises in patients with muscle weakness are influenced by intramuscular pathology including muscle morphology, mitochondrial function, and systemic inflammation, based on their disease pathology, potentially requiring personalized training schedules.

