**Discussion:**

This study will explore differential responses to muscle endurance and muscle strength exercises in patients with RA, OA, and SARC, offering novel insights into the molecular mechanisms of muscle weakness. The findings may help identify potential mechanisms underlying variability in exercise response and provide effect size estimates to guide future confirmatory studies and more targeted exercise interventions.

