In RA, muscle weakness cannot be attributed to a decrease in muscle mass alone but is most likely also linked to impaired mitochondrial functioning mediated by chronic systemic inflammation [3,17–19]. While muscle weakness is known to be present in OA patients, the underlying causes and the pathophysiology are still unclear [20]. In SARC, muscle weakness is associated with increased muscle wasting [21,22] and decreased sensitivity to protein synthesis (anabolic resistance) [23]. Endurance exercises, generally conducted at lower intensities (30% to 50% of 1RM) and performed to volitional failure, has been shown to improve local muscular endurance and stimulate mitochondrial adaptations, thereby increasing oxidative capacity within skeletal muscle [24–26]. In contrast, strength exercises, typically performed at intensities ranging from 60% to 90% of one-repetition maximum (1RM), [24] has been shown to promote myofibrillar protein synthesis [27–30]. The optimal loading strategy for combating muscle weakness in diseases with distinct muscle pathologies such as RA, OA, and SARC remains to be investigated.

Although RA, OA and SARC represent distinct clinical entities, they all present with reduced muscle strength and impaired physical functioning. The mechanisms underlying muscle weakness are, however, expected to differ between these conditions, ranging from chronic systemic inflammation in RA, to local joint-related and low-grade inflammatory processes in OA, and age-related muscle degeneration in sarcopenia [12]. These differences in underlying muscle characteristics may contribute to the substantial inter-individual variability observed in response to exercise and highlight the need for a better understanding of mechanism-based exercise approaches [16]. Therefore, this study aims to compare the effects of strength and endurance exercise and explore the association between muscle characteristics and exercise outcomes in patients with RA, OA and SARC. We hypothesize that responses to endurance and strength exercises in patients with muscle weakness are influenced by intramuscular pathology including muscle morphology, mitochondrial function, and systemic inflammation.

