## Methods

### Study design

This study is a two-arm parallel-group exploratory trial. Participants will be randomized using a minimization procedure for allocation to either the muscle endurance or muscle strength exercise group (see section Randomization, blinding and allocation concealment). Assessments will be conducted at baseline and after 8 weeks (Fig 1) of intervention (post-treatment). Exercise training will be delivered at the outpatient clinic at Reade, center for rehabilitation and rheumatology in Amsterdam, as part of regular clinical care.

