#### 2. Secondary outcome (Associations between muscle characteristics and exercise response).

i) Linear regression analyses will be conducted for each characteristic, e.g., muscle morphology (marker: DSM-BIA, physiological cross-sectional area and pennation angle), mitochondrial function (marker: Basal respiration; Leak respiration; NADH-linked respiration, Succinate-linked respiration, Maximal Oxidative Capacity; Maximum uncoupled respiration), and inflammation (markers: IL-6; IFN-γ; IL-17; IL2; IL-4; IL-10 and TNF-α). The change in muscle strength (T1 – T0) will be the dependent variable, and each muscle characteristic will serve as the independent variable.ii) To explore whether associations between muscle characteristics and exercise response differ by exercise modality, models will be extended by including exercise group and interaction terms (muscle characteristic × exercise group). Given the exploratory nature of the study and the limited sample size, these analyses are intended to identify potential signals rather than provide definitive evidence of effect modification. Interaction estimates will be interpreted cautiously, with emphasis on estimated effect sizes and 95% confidence intervals rather than statistical significance testing.iii) Adjusting for covariates. All models will be adjusted for the minimization factors (gender and disease type) and prespecified covariates (age and BMI). Given the exploratory nature of the study and the available sample size, the number of covariates will be restricted to reduce the risk of model overfitting..iv) Aforementioned steps will be repeated with other clinical outcomes (isokinetic muscle endurance, 6MWT, SPPB physical function and pain) as the dependent variables to address the secondary objective of the study.

Missing data will be addressed using the Multivariate Imputation by Chained Equations (MICE) method when data were assumed to be Missing Completely at Random (MCAR) or Missing at Random (MAR). Variables with substantial missingness (>30%) or data deemed Missing Not at Random (MNAR) will be excluded. Analyses on imputed data will be compared with the original dataset to assess consistency.

Analyses will be based on the intention-to-treat principle (ITT), in which data of all participants will be analyzed according to group assignment. In addition, per-protocol analysis will be performed including only those participants that performed 80% or more sessions.

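### As written, the primary mixed model gives an unadjusted difference in mean change: disease and gender main effects cancel, and baseline torque is not used

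*Protocol article*

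**What the plan says.** Protocol article, Data analysis plan, item 1 (primary outcome): "Models will include fixed effects for exercise group, time (pre/post), exercise group, disease type, and gender". Exercise group is listed twice. The only interaction named is time × exercise group: "The time × exercise group interaction will be included to estimate differential changes in muscle strength between intervention groups". On the covariance side the text says "Random effects will account for individual variability". No baseline covariate and no common-baseline constraint is mentioned.

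Study design gives two measurement occasions: "Assessments will be conducted at baseline and after 8 weeks". The section on randomization makes disease and gender the minimization factors.

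Item 2 (associations with muscle characteristics) uses a change score: "The change in muscle strength (T1 – T0) will be the dependent variable". Those regressions are adjusted for gender, disease, age and BMI, and step (ii) adds exercise group and its interaction with each characteristic.

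The Background states the aim: "this study aims to compare the effects of strength and endurance exercise and explore the association between muscle characteristics and exercise outcomes". The abstract's Discussion adds: "This study will explore differential responses to muscle endurance and muscle strength exercises in patients with RA, OA, and SARC".

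**The concern.** A reader who sees disease and gender in the primary model will take the arm comparison to be adjusted for the minimization factors. With two visits it is not. Terms that are constant over time shift a participant's level at both visits equally and drop out of the change. Leaving the arms free to differ at baseline also turns the analysis into a plain comparison of change scores, so the most informative covariate available, baseline torque, does no work.

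The Trial sample size section says that N was set by feasibility and that the purpose is to estimate effects and variability. Precision is therefore the main product of the trial, and some of it is given up although the data are already collected. Separately, the stated models contain no term from which a difference between diseases in the strength-versus-endurance effect could be read.

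**Working it through.** **Inputs.** From the document: two visits; the fixed effects quoted above; 60 analysed, 30 per arm (Trial sample size; 60 × 1.15 = 69 reproduces the enrolment target, and nothing below depends on it). Assumed, because the document gives no figure: pre-post correlation r from 0.5 to 0.9; equal SD at both visits; a random intercept per participant; about 20 analysed per disease, split 10 v 10.

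**Step 1: what the interaction estimates.** For participant i in arm A:

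- baseline: μ + αA + disease + gender + uᵢ + e₀
- follow-up: μ + αA + disease + gender + uᵢ + τ + βA + e₁
- change: τ + βA + (e₁ − e₀)

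Disease, gender, the baseline arm effect α and the random intercept all cancel. With complete data, β is the difference in mean change.

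**Step 2: check by simulation.** 53 participants with unequal arms, and disease and gender affecting both level and change.

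| Analysis | Time × group estimate (SE) |
|---|---|
| With disease and gender main effects | 0.16815 (0.17010) |
| Without them | 0.16815 (0.17010) |
| Raw difference in mean change | 0.16815 |
| With disease × time and gender × time | 0.2029 (0.1748) |

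Only the last row adjusts the contrast. In this data set the added terms moved the estimate without reducing its SE. With 8 follow-up values missing, the main effects moved the estimate only from 0.2734 to 0.2644.

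**Step 3: cost of not using baseline torque.** In units of the outcome variance, the variance per participant is 2(1 − r) for a change score and 1 − r² for ANCOVA. The ratio is 2(1 − r)/[(1 − r)(1 + r)] = 2/(1 + r). The effective sample lost is 1 − (1 + r)/2 = (1 − r)/2. The 95% CI half-width at 30 per arm is 1.96 × √(variance × 2/30).

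| r | Variance ratio | SE larger by | Effective sample lost | Half-width, change score (SD) | Half-width, ANCOVA (SD) |
|---|---|---|---|---|---|
| 0.5 | 1.33 | 15% | 25% | 0.506 | 0.438 |
| 0.7 | 1.18 | 8% | 15% | 0.392 | 0.361 |
| 0.8 | 1.11 | 5% | 10% | 0.320 | 0.304 |
| 0.9 | 1.05 | 3% | 5% | 0.226 | 0.221 |

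**Step 4: chance baseline imbalance.** A one-SE difference between arms at baseline is √(2/30) = 0.26 SD. The change-score estimate differs from the ANCOVA estimate by (1 − r) times that imbalance: 0.13 SD at r = 0.5 and 0.08 SD at r = 0.7.

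**Step 5: what a disease × arm estimate would deliver.** Using the change-score variance, the half-width within one disease (10 v 10) is 1.96 × √(2(1 − r) × 2/10): 0.68 SD at r = 0.7 and 0.55 SD at r = 0.8. For the difference in arm effect between two diseases, multiply by √2: 0.96 and 0.78 SD.

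**The case against.** Several counter-arguments carry weight.

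- *The contrast is valid.* A reader might infer that the primary estimate is biased. It is not: under randomization the change-score contrast is unbiased on average. Imbalance matters only in the sample that happens to be realised.
- *The loss may be small.* It is 3–8% in SE for r between 0.9 and 0.7, and r is wholly assumed. A reader might also turn the ratio of 1.33 into a third of the sample lost. It means 33% more patients needed, or 25% of effective sample lost.
- *Minimization already balances disease and gender*, so little imbalance in them remains to be removed, and with dropout the main effects do a little. This stands, but it does not make the adjustment that the model appears to contain effective. Nor does the adjustment statement in item 2 help if it is read as covering the primary model: age and BMI as main effects would cancel in the same way.
- *Disease-specific response is not the trial's main question.* It is tempting to say that the model cannot answer the headline aim. The stated aim is the overall arm comparison plus associations with muscle characteristics, and the primary model does estimate the former. The abstract's hypothesis speaks of responses "based on their disease pathology, potentially requiring personalized training schedules", which makes disease an exploratory purpose. The abstract sentence on differential responses can also be read as describing the study population. Disease is partly handled elsewhere: results are described by diagnosis, and disease is a covariate in the item 2 change-score regressions, which acts there like disease × time. The trial also disclaims powered within-disease analyses.
- *The article is condensed.* Exploratory disease-specific models may be in a document not shown, and the repeated exercise group may stand where another term was meant. The text cannot settle this. The primary model, however, is stated, and as stated it has the properties shown above.

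**Conclusion.** The point holds as one of precision and clarity. The stated primary model yields the unadjusted difference in mean change: exactly so with complete data, very nearly so with dropout. Against a baseline-adjusted analysis it has a 3–15% larger SE, equivalent to losing 5–25% of effective sample size, for r from 0.9 to 0.5 and equal variances at the two visits. Chance baseline imbalance passes into the estimate. Validity under randomization is not in question.

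Secondarily, disease × exercise group is absent from every stated model, although the abstract promises to explore differential responses and the main Discussion refers to disease-specific analyses. That is a gap between an exploratory purpose and the stated models, not a failure of the primary aim.

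**What to change.** 1. Analyse follow-up torque by ANCOVA on arm, baseline torque, disease and gender. Equivalently, keep the mixed model but constrain the arms to a common baseline mean and add disease × time and gender × time.
2. Remove the duplicated exercise group, or replace it with the term that was intended.
3. Add one exploratory model with disease × arm (× time in the mixed model), labelled as not powered. Report the arm contrast within each disease and also the differences in arm effect between diseases, with 95% CIs. Three within-disease contrasts alone do not show whether the diseases differ.

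Baseline torque should not be added to the step (ii) characteristic × arm models as part of this change. It may be closely related to muscle morphology such as PCSA, so conditioning on it would change what those coefficients mean.

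The cost is wording and a few parameters; no new data are needed. The gain in item 1 comes mainly from baseline torque, since minimization leaves little disease or gender imbalance to remove. The intervals in item 3 will be visibly wide, and the text should say so beforehand.

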### Physiotherapists and training

Six physiotherapists from Reade, all experienced in treating patients with rheumatic diseases, will be trained to deliver the standardized exercise program. Prior to the start of the trial, the physiotherapists will complete a mandatory, comprehensive two-hour training session. The training includes an explanation of the intervention protocol and study procedures, followed by a one-hour practical session to familiarize the physiotherapists with the use of the training equipment and performing an adequate 10 repetition maximum (10 RM) test. Interim training sessions will be held during the trial to control and optimize the quality of the interventions.

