### Intervention

The intervention consists of an 8-week exercise program. Participants will be randomized into the endurance or strength exercise group. Each week, participants complete three exercise sessions: two supervised by PTs in groups of max. four participants and one performed independently at home. Each session includes 6–8 full-body exercises from a predetermined list: three quadriceps-focused exercises, one hip or glute exercise, and two upper body exercises as appropriate (see S1 File). Exercises are performed using the Reforter™ (HapticLink, The Netherlands), fitness equipment (e.g., leg press), and resistance bands. The Reforter™ is an electronic pulley cable system that allows for: 1) concentric and eccentric muscle loading; 2) force adjustment based on position, speed, or reaction force; 3) instantaneous measurements of force [N], speed [m/s], position [m], power [W], and work [J]. The software allows for various settings and programs specific to endurance and strength focused training and provides feedback during the exercises. Physiotherapists use this data to tailor and adjust training loads.

After familiarization with the correct execution of exercises (week 1, initial three sessions), a 10-repetition maximum (RM) test will be performed for the exercises conducted on regular fitness equipment. The 10RM results are used to calculate the estimated 1RM using the Brzycki formula [34]. This process will be repeated in week 5, after which training intensity will be adjusted, and again in week 8.

Supervised sessions include a 5–10 min warm-up and a 5 min cool-down, with total session duration ranging from 45 to 60 minutes. All participants will perform the same exercises at an intensity of a of 7–8 on a 10-point physical exertion scale (see Additional file 1 supervised exercise).

The endurance group performs the exercises with a load of 30–45% of their 1RM, while the strength group performs the exercises with a load of 60–75% of their 1RM. For further details on sets, repetitions, and rest time, see Table 2.

**Table 2 pone.0356181.t002:** Exercise intervention of the supervised and home-based training for both endurance and strength group.

	Frequency	Intensity	Time
**Strength group**	2x/week at Reade/ supervised	10 repetitions 3 sets 90s rest between sets 60-75% 1RM	45-60mins (incl. warm-up & cool down); Progressive
	1x/week home-based/unsupervised	10 repetitions 3 sets	30 mins

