**Endurance**					
Weeks 1–2	3	20	30% 1RM	3 sets * 20 reps * 30 kg	1800
Weeks 3–4	3	20	35% 1RM	3 sets * 20 reps * 35 kg	2100
Weeks 5–6	3	20	40% 1RM	3 sets * 20 reps * 40 kg	2400
Weeks 7–8	3	20	45% 1RM	3 sets * 20 reps * 45 kg	2700

RM: repetition maximum.

To guarantee safety, tolerability will be assessed in each session using a numerical rating scale for pain (NRS, scale 0–10) or, where appropriate, physical examination. For NRS > 5, training load is modified. PTs may provide tailored instructions during sessions, following the same procedure for both groups.

The home-based exercises are initially taught at Reade and consist of bodyweight and resistance bands exercises. Exercise selection is the same across groups. However, the strength group uses bands with greater resistance. Additionally, repetition counts and rest intervals mirror those used in supervised sessions. Patients are instructed to target an intensity of 7–8 on a 10-point physical exertion scale. To ensure adherence to the intended intensity level, patients are asked to be aware of effort using easily measurable physiological indicators such as breathing rate, perspiration, and muscle soreness. Exercises are regularly evaluated and adjusted as needed by the treating physiotherapist.

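### The primary model as described has no term for training group or physiotherapist; if these are arm-specific and strength changes correlate within them, the interval for time × exercise group is too narrow

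*Protocol article*

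**What the plan says.** The Intervention section sets three sessions a week for eight weeks, "two supervised by PTs in groups of max. four participants and one performed independently at home". On staffing, the section on physiotherapists and training states: "Six physiotherapists from Reade, all experienced in treating patients with rheumatic diseases, will be trained to deliver the standardized exercise program". The physiotherapists use device data to set and change loads, and they review the home exercises. After Table 3 the article adds: "PTs may provide tailored instructions during sessions, following the same procedure for both groups".

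The primary analysis is a linear mixed model. Its fixed part is given as "Models will include fixed effects for exercise group, time (pre/post), exercise group, disease type, and gender", followed by "The time × exercise group interaction will be included to estimate differential changes in muscle strength between intervention groups". Its random part is one sentence: "Random effects will account for individual variability". No training-group or physiotherapist term and no cluster-adjusted standard error is named there or in the secondary regressions.

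The article does not say whether a training group holds one arm or both, whether groups are closed or rolling, or whether each physiotherapist treats both arms. It gives no ICC. Under Trial sample size it explains that "no reliable disease-specific between-group effect size was available to perform a formal a priori sample size calculation for the primary comparison", and it describes the trial's purpose as estimating effects, variability and associations for the design of later confirmatory trials.

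**The concern.** Patients who train together, or under the same physiotherapist, share coaching, pacing and decisions about load. Their changes in strength may therefore be correlated. A participant-level random effect captures the correlation between one person's two measurements. It does not capture correlation of change between different people in the same delivery unit.

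Where the delivery unit lies wholly within one arm, that shared variation stays in the arm difference, and the model treats it as if it averaged out over independent patients. The interval is then too narrow. This matters even in an exploratory trial, because effect and variability estimates for later trials are its stated product. Without recorded unit membership, neither the size of the problem nor its absence can be shown afterwards.

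**Working it through.** **The plan's own figure.** The target of 69 is 60 × 1.15 = 69. Taking 15% off 69 leaves 69 × 0.85 = 58.65, close to the stated 60. Neither step involves clustering, and the plan gives no power, standard deviation or ICC. I use 60 analysed, 30 per arm.

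**Inputs.** Group size m is at most 4 (Intervention). There are six physiotherapists (Physiotherapists and training). The ICC of change is an assumption, 0 to 0.10. The unit-by-arm structure is not stated, so each possibility is worked through.

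**Formulas for units lying within one arm.** Design effect DE = 1 + (m − 1) × ICC. True SE / reported SE = √DE. Effective sample = 60 / DE. Coverage of a nominal 95% interval = 2Φ(1.96/√DE) − 1.

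| Structure | ICC | DE | SE factor | Effective N | Coverage |
|---|---|---|---|---|---|
| Any | 0 | 1.00 | 1.000 | 60 | 95.0% |
| Fixed groups of 4, arm-specific | 0.01 | 1.03 | 1.015 | 58.3 | 94.7% |
| | 0.05 | 1.15 | 1.072 | 52.2 | 93.2% |
| | 0.10 | 1.30 | 1.140 | 46.2 | 91.4% |
| Physiotherapists arm-specific (3 per arm, 10 patients each) | 0.01 | 1.09 | 1.044 | 55.0 | 94.0% |
| | 0.05 | 1.45 | 1.204 | 41.4 | 89.6% |
| | 0.10 | 1.90 | 1.378 | 31.6 | 84.5% |

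Smaller groups reduce the effect. At ICC 0.10, groups of three give DE 1.20 and coverage 92.6%, and groups of two give DE 1.10 and coverage 93.8%.

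**Simulation.** I simulated 20,000 trials per setting, 30 per arm, with a t-test on change that ignores units. With complete pre and post data this stands in for the time × exercise group contrast. Actual error of a nominal 5% test:

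| Structure | ICC 0.05 | ICC 0.10 |
|---|---|---|
| Arm-specific groups of four | 6.6% (formula 6.8%) | 8.5% (formula 8.6%) |
| Arm-specific physiotherapists | 10.3% (formula 10.4%) | 15.8% (formula 15.5%) |
| Groups of four with both arms | 4.4% | 4.0% |
| Each physiotherapist treating both arms equally | 4.7% | 4.2% |

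In the last two rows the shared component cancels from the arm difference but stays in the residual variance. The reported SE is then slightly too large: true/reported is 0.95 to 0.96 at ICC 0.10. One exception is a physiotherapist effect that itself differs by arm. Six physiotherapists × 2 arms gives cells of 60/12 = 5 patients, and if such variance had a share of 0.10, DE = 1 + 4 × 0.10 = 1.40 and coverage is 90.2%.

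**How likely closed groups of four are.** Recruitment from January 2026 to August 2027 is about 87 weeks. If it is even, 69 × 8/87 ≈ 6.3 patients are in training at any time, or about 3.2 per arm, at staggered weeks.

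**How well the ICC could be estimated.** For 60/4 = 15 groups and a true ICC of 0.05, the large-sample SE is (1 − 0.05)(1 + 3 × 0.05)√[2/(4 × 3 × 14)] = 0.95 × 1.15 × 0.109 ≈ 0.12, so the 95% interval is about ±0.23.

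**The case against.** The strongest reply is that nothing here is shown to be an error. A reader might infer that the standard error is wrong whichever way groups are formed. The article does not support that: at ICC 0 there is no error, no ICC is given, and the direction depends on a structure that is not described. Nor does the article say that the random effects are for individuals only. It is a condensed account, and an unseen analysis plan may add terms. That physiotherapists follow one procedure in both arms is compatible with each of them treating both. With about six patients in training at once, closed arm-specific groups of four sharing all eight weeks would rarely form. Loads are scaled to each patient's own maximum, fidelity is reviewed, and outcome assessors are blinded, all of which limit shared effects.

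A second reply concerns the remedy. A group term in the primary model could take the degrees of freedom from about 58 to about 13 (15 groups less 2). The critical t then rises from 2.00 to 2.16, an interval up to 8% wider, which is about the 7.2% understatement that it would correct at ICC 0.05. With rolling membership there may be no stable group to fit.

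Both replies stand as far as they go. They rule out the unconditional claim and argue against changing the primary model. They do not remove the point. The article does state what the random effects are for, that purpose is individual-level, and delivery is shared by design. Whether the interval is sound depends on facts that the trial can record but, as described, does not.

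**Conclusion.** The point holds conditionally, as a cheap improvement. The primary model as described carries no term for the unit in which training is delivered. If groups are fixed and arm-specific, with four patients and an ICC of change between 0.01 and 0.10, the true SE of the time × exercise group contrast is 1.5% to 14% larger than reported, and coverage is 94.7% to 91.4%. Arm-specific physiotherapists would make this worse. Mixed-arm groups, or physiotherapists treating both arms, leave the interval about right or slightly too wide, unless a physiotherapist's effect differs by arm. The ICC range and the structures are assumptions. The target of 69 is not affected.

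It would also go too far to say that the trial could supply a usable ICC for later planning: with about 15 groups the estimate would be very imprecise.

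**What to change.** - Record each participant's training group, or session attendance if groups are rolling, and the main treating physiotherapist. The physiotherapists' logbooks and the electronic case report form already exist for this.
- State how training groups and physiotherapists map to arm.
- Keep the primary model, and prespecify a sensitivity analysis of the time × exercise group contrast with a random effect on change for training group (or for physiotherapist if groups are rolling), using small-sample degrees of freedom.
- Report the variance component with its interval, and describe it as imprecise.

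The cost is one or two data fields, one extra model, and a wider interval in that sensitivity analysis. The recording should start as early in recruitment as possible, because group membership may be hard to reconstruct later.
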